##### Participants’ Satisfaction

Finally, the intervention group participants’ perception of the quality of the exercise program will be investigated, as it strongly influences the adherence to an exercise program [42]. It will be verified by a dedicated questionnaire with structured responses based on a 7-point Likert scale [88,89,90].

### 2.8. Statistical Analysis

The qualitative variables will be summarized in terms of frequency, and the quantitative ones in terms of mean and standard deviation for both intervention groups and control groups and for the three times of assessment. To compare characteristics between and within groups the principle of intention to treat will be used, adjusting for adherence to the exercise program. In order to compare the baseline characteristics between the two groups, the following tests will be used: Student’s t-test for parametric quantitative variables; Mann–Whitney test for non-parametric variables; Chi-square test for qualitative dichotomous variables. To compare the changes between and within intervention groups and control groups among baseline and follow-up assessments the following tests will be used: for the normally distributed variables, analyses of variance for repeated measures followed by t-test with Sidak post hoc corrections; for non-parametric variables, the Friedman test followed by the Wilcoxon test with Bonferroni correction.

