### 2.4. Sample Size

The sample size was calculated through an a priori power analysis calculated on the study’s primary outcome, the physical health domain of the 36-item Short Form Health Survey (SF-36), assessed at post-surgery baseline and six-month assessments in both intervention and control groups. A randomized controlled pilot study in the literature with a similar rationale [36] was considered as a reference. Starting from this study, in which the SF-36 was used before and three months after the start of the intervention, was found a size effect of 1.06 (considered “increased”) with a standard deviation of 10 for each considered group. The power analysis was performed separately for THR and TKR, using a two-code test for independent groups with an error α = 0.05 and a sampling power (1-β) of 0.8, and a drop-out percentage of 30%. The minimum number required was estimated in 20 patients per group. Considering the four groups evaluated in the present study, two intervention groups (THR or TKR) and the two respective control groups, the final sample size was identified in a total of 80 patients.

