#### 2.7.2. Primary Outcome

The primary outcome is QoL’s modification, measured with the SF-36 [44,45,46]. SF-36 is one of the most widely used questionnaires to measure the health-related QoL in total hip and total knee arthroplasty patients [47]. SF-36 is composed of 36 items and is focused on measures of two main domains: physical and mental health. It is a multi-item scale that assesses eight health concepts [44]: (1) limitations in physical activities caused by health problems; (2) limitations in social activities because of physical or emotional problems; (3) limitations in usual role activities because of physical health problems; (4) body pain; (5) general mental health (psychological distress and well-being); (6) limitations in usual role activities because of emotional problems; (7) vitality (energy and fatigue); (8) general health perceptions. Validity and reliability of SF-36 have been previously proved also for the Italian version of the questionnaire [48].

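### The test for the primary SF-36 outcome depends on its distribution, and the rank-based route contains no evident comparison between the arms

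*Protocol article*

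**What the plan says.** Section 2.8 of the protocol article opens its rule for change with a general scope: "To compare the changes between and within intervention groups and control groups among baseline and follow-up assessments the following tests will be used". Two routes follow. The first route, and the split that leads to the second, read "for the normally distributed variables, analyses of variance for repeated measures followed by t-test with Sidak post hoc corrections; for non-parametric variables". The second route in full is "for non-parametric variables, the Friedman test followed by the Wilcoxon test with Bonferroni correction". The section gives no criterion for normality, no scale on which to judge it (score or change) and no unit (arm, visit, joint or pooled).

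Section 2.7.2 defines the primary outcome: "The primary outcome is QoL’s modification, measured with the SF-36". Neither section says which route it takes.

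Section 2.4 is more definite. It sizes the trial on "the physical health domain of the 36-item Short Form Health Survey (SF-36), assessed at post-surgery baseline and six-month assessments", "using a two-code test for independent groups with an error α = 0.05", with power 0.8 and 30% drop-out, doing the calculation for each joint in turn. The result is 20 per group and 80 in all.

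**The concern.** The sample size rests on one comparison, intervention against control. The analysis section does not carry that comparison forward as the fixed primary test. It gives a conditional rule, and the natural reading is that the condition is checked on the outcome data.

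The larger problem is what the second route tests. A Friedman test ranks each patient's visits against each other and has no term for treatment arm. The Wilcoxon test that follows it reads as the paired version, because the same section names Mann–Whitney when it wants a two-group rank comparison (for baseline characteristics). On that reading the route yields one set of visit-to-visit p-values for each arm and nothing that compares the arms. An effect claim would then rest on one arm reaching significance and the other not, which is not a test of the randomised difference.

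**Working it through.** **1. The plan's own figure.** Inputs from section 2.4: "was found a size effect of 1.06 (considered “increased”) with a standard deviation of 10 for each considered group", two-sided α = 0.05 (reading the garbled term as two-tailed), power 0.80, drop-out 30%.

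- Normal approximation: n = 2(1.960 + 0.842)² / 1.06² = 15.70 / 1.1236 = 13.97, so 14 evaluable per group. 14 / 0.70 = 20 enrolled.
- Exact t-test: 14.99, so 15 evaluable. 15 / 0.70 = 21.4, so 22 enrolled; or 15 × 1.30 = 19.5, so 20.

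The stated 20 per group is reproduced as a two-arm comparison of means. No number in section 2.4 is disputed.

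**2. What each route tests.**

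| Route in section 2.8 | Compares visits within patients | Compares change between arms |
|---|---|---|
| Repeated-measures ANOVA, then t-tests | yes | possible, through the arm-by-time term |
| Friedman, then Wilcoxon | yes | none evident |
| Test used for sizing (section 2.4) | no | yes |

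**3. What the second route does when the arms do not differ.** Simulation of 2,000 trials per setting: two arms, three visits, normal data, correlation 0.5 between visits. Both arms have the same true improvement, with 60% of it reached at 3 months. An arm counts as significant if Friedman p < 0.05 and the baseline-to-6-month Wilcoxon p < 0.05/3.

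| True improvement in both arms (SD of change) | Significant in intervention arm only, 14 per arm | Same, 20 per arm |
|---|---|---|
| 0 | 1.2% | 1.1% |
| 0.3 | 4.5% | 7.9% |
| 0.5 | 14.2% | 19.0% |
| 0.7 | 21.6% | 23.9% |

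The two arms disagreed in either direction in 10% to 49% of trials across the 0.3 to 0.7 rows.

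**4. How often the second route would be chosen.** This depends on a check the protocol does not state. Assume Shapiro-Wilk at 0.05 in each arm of one joint, with either rejection triggering the rank route. With truly normal data the expected frequency is 1 − 0.95² = 9.8%; simulation (4,000 runs) gave 10.0% with 14 per arm and 9.5% with 20. With mild skew it was 35% to 49%, and with stronger skew or a ceiling 60% to 82%. A single check per joint on pooled residuals would flag about 5% of normal data sets.

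**5. Type I error of switching as such.** If the choice were between two valid between-arm tests (t-test or Mann–Whitney) under the same Shapiro-Wilk rule, the error rate was 4.7% to 5.6% across all distributions tried, against a nominal 5%.

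**The case against.** The strongest reply is that this is a condensed article. The full protocol or an analysis plan may class the SF-36 in advance, and section 2.8 never says in words that normality is judged on this trial's data. The last part is correct: it is the natural reading, not a stated fact. But the article is not silent. It states a rule covering all comparisons of change, and a later document that fixed one SF-36 test would have to override it.

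A second reply is that Wilcoxon might mean the rank-sum test. Placed after Friedman, in a section that uses Mann–Whitney for two groups, this is the less likely reading. If it was intended, the between-arm comparison would not be lost, but the primary test would still not be fixed.

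Three stronger readings are tempting and should not be drawn:

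- **Hips and knees will get different primary tests.** Only the power calculation is stated to be separate by joint. Section 2.8 classifies variables, not joints. If the SF-36 is classed once, the joints cannot diverge.
- **The false-positive rate is materially inflated by the switch.** Step 5 shows it is not. A larger figure needs the analyst to run both tests and keep the smaller p-value, which section 2.8 does not permit.
- **A quarter or more of trials would be misrouted under normality.** That needs a check in all six arm-by-visit cells, with any single rejection decisive (1 − 0.95⁶ = 26.5%). The protocol describes no such check.

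**Conclusion.** The point holds as one of pre-specification and of what is being tested. Section 2.8 leaves the primary SF-36 test conditional on the distribution, and one of its two routes does not evidently compare the randomised arms. If that route is taken and read arm by arm, equal true improvement of 0.3 to 0.7 SD of change in both arms appears as an effect confined to the intervention arm in about 5% to 24% of trials. That range assumes normal data, 14 or 20 per arm, correlation 0.5 between visits and a paired Wilcoxon test. How often the route would be taken cannot be derived from the documents; about 10% per joint for normal data is conditional on the assumed arm-wise Shapiro-Wilk check. The sample size stands. The rule should be changed before outcome data are analysed.

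**What to change.** In section 2.8, take the SF-36 physical domain (the outcome used for sizing) out of the normality rule and name one primary analysis, used whatever the distribution: the between-arm mean difference at 6 months adjusted for the post-surgery baseline score, by ANCOVA or the equivalent contrast from the repeated-measures model. Add, as a fixed sensitivity analysis, a permutation p-value for that same contrast. Within-arm visit comparisons can remain as description.

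The cost is one sentence and a few lines of code, with no change to visits or data. The requirement stays at 14 to 15 evaluable, or 20 to 22 enrolled per group. Fixing a rank-based between-arm test instead would not be free: at relative efficiency 0.955 (normal data) to 0.864 (worst case), 14.99 / 0.955 = 15.7 and 14.99 / 0.864 = 17.3, so 16 to 18 evaluable. Dividing by 0.70 gives 23 to 26 enrolled per group.

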### Limitation

The final goal of this study is to increase regular physical activity among the persons who underwent THR/TKR. Thus, to detect modifications of lifestyle activity represents an important goal of our project. However, to measure lifestyle activity is not an easy matter and several methods have been proposed including self-report questionnaires, smart phone technology, motion sensors, and pedometers [115]. All these methods have strengths and limitations in terms of methodological effectiveness and feasibility. The use of wearable devices or smart phones can be accurate but not easy to use in long-term study by aged participants. Thus, we decided to use a self-report questionnaire of physical activity (RPAQ) and weekly logs although social desirability may result in over-reporting of PA among participants keen to comply with the intervention aims [116]. These factors will require careful consideration in the interpretation of the results.

The protocol takes into account the duration and number of sessions of rehabilitation which participants have undergone before and after surgery, but not the type and intensity of this treatment. This may weaken the results of the study, as large and consistent evidence has proved the importance of pre- and post-surgery rehabilitation [43]. However, we deemed it unfeasible to reliably control this variable, as rehabilitation treatment will be performed not within the premises of our hospital but at the community level within private or public facilities. Nonetheless, differences in rehabilitation treatment outcomes observed at the post-surgery baseline will be used in the results’ analysis and interpretation.

We excluded people from participation in the study who are unable to walk unassisted for 500 m or have significant pain at rest. This may limit the participation of people who need the exercise the most and weaken the study conclusions. However, people with important functional limitations and/or severe pain are eligible for medical and rehabilitation care or aquatic exercise programs while land-based group exercise could be very problematic or even unsafe.

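### Section 2.8 does not carry out the comparison that Section 2.4 powers: no 6-month between-arm contrast is named as primary, and post-surgery baseline SF-36 is not used as a covariate

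*Protocol article*

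**What the plan says.** Section 2.4 takes as primary outcome the physical health domain of the SF-36, "assessed at post-surgery baseline and six-month assessments in both intervention and control groups". The sample size was computed "using a two-code test for independent groups with an error α = 0.05 and a sampling power (1-β) of 0.8". The effect came from a pilot trial "in which the SF-36 was used before and three months after the start of the intervention"; there "was found a size effect of 1.06", "with a standard deviation of 10 for each considered group". On strata: "The power analysis was performed separately for THR and TKR". With 30% drop-out this gives 20 per group and 80 in total.

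Section 2.8 sets one generic procedure for changes between and within groups across baseline and follow-up. Normally distributed variables get "analyses of variance for repeated measures followed by t-test with Sidak post hoc corrections"; the others get Friedman and then Wilcoxon tests with Bonferroni correction. It singles out neither the group-by-time term nor the 6-month visit for SF-36, and it does not give the number of corrected comparisons. Intention to treat is the stated principle. Adherence is the only adjustment variable named.

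The Limitation subsection of the Discussion says that "differences in rehabilitation treatment outcomes observed at the post-surgery baseline will be used" in analysis and interpretation, but Section 2.8 contains no model that does this.

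**The concern.** A sample size justifies a trial only for the test it was computed for. Here the computation is for one uncorrected two-group test, while the analysis is an omnibus test over three assessments followed by multiplicity-corrected t-tests. The 0.80 in Section 2.4 therefore does not describe the procedure in Section 2.8, and a reader cannot tell which result decides the trial.

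SF-36 is also recorded before randomisation (Section 2.1 and Table 2). With 20 per group, chance imbalance at baseline is quite possible. Using the baseline score as a covariate would deal with that and usually sharpen the comparison, with data already being collected.

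**Working it through.** **Inputs from Section 2.4:** d = 1.06, SD 10, alpha 0.05 (read as two-sided), power 0.80, drop-out 30%, each joint separately.

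**Assumed, because the document does not give them:** the correlation r between assessments (0.3, 0.5, 0.7, equal between all pairs); the 3-month effect (half or all of the 6-month effect); the number m of Sidak-corrected comparisons.

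**1. The plan's own figure.** n = 2(1.960 + 0.842)²/1.06² = 13.97, so 14 per group; 14/0.70 = 20. The stated 20 is reproduced, for the single uncorrected two-group test.

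**2. Powered test, exact.** Noncentral t, noncentrality 1.06 × √(14/2) = 2.804, 26 df: power 0.77. The normal approximation gives 0.80. This gap comes from the approximation, not from Section 2.8.

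**3. Sidak-corrected 6-month t-test.** Per-test alpha = 1 − 0.95^(1/m), same noncentrality.
- m = 2: alpha 0.0253, power 0.67
- m = 3: alpha 0.0170, power 0.60

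**4. Group-by-time F test**, 2 and 52 df. The noncentrality is (n/2) × (sum of squared deviations of the three between-arm differences from their mean)/(1 − r), in SD units.
- Half effect at 3 months, differences 0, d/2, d: n·d²/[4(1 − r)] = 5.62, 7.87, 13.11 at r = 0.3, 0.5, 0.7
- Full effect at 3 months, differences 0, d, d: n·d²/[3(1 − r)] = 7.49, 10.49, 17.48

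**5. Baseline-adjusted 6-month contrast (ANCOVA)**, 25 df. The noncentrality is 2.804/√v, where v is the residual variance relative to the SD of 10.
- If 1.06 refers to the follow-up score, v = 1 − r² = 0.91, 0.75, 0.51.
- If 1.06 refers to change, the follow-up variance is 100/[2(1 − r)], so v = (1 − r²)/[2(1 − r)] = (1 + r)/2 = 0.65, 0.75, 0.85.

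| Power, 14 per arm | r = 0.3 | r = 0.5 | r = 0.7 |
|---|---|---|---|
| F test, half effect at 3 months | 0.53 | 0.68 | 0.89 |
| F test, full effect at 3 months | 0.66 | 0.81 | 0.96 |
| ANCOVA, 1.06 is follow-up score | 0.80 | 0.87 | 0.96 |
| ANCOVA, 1.06 is change | 0.92 | 0.88 | 0.83 |

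The F-test rows take 1.06 as the follow-up score. If it is change, d² is multiplied by 2(1 − r), r cancels, and the F test has 0.68 or 0.81 throughout. The ANCOVA figures are good to about 0.015: dividing the noncentrality by √(1 + 1/24), to allow for chance baseline imbalance, lowers them slightly (for example 0.79, 0.86, 0.96 in the third row).

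**6. Where the gain disappears.** On the follow-up reading with that allowance, ANCOVA has 0.769 at r = 0.2 and 0.752 at r = 0, against 0.770 for the unadjusted t-test.

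**The case against.** Several counter-arguments have weight.

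- **Baseline is not ignored.** It is one level of the repeated factor, a group-by-time test works on within-person change, and the Limitation subsection mentions using baseline differences. This stands. What is absent is its use as a covariate.
- **Low power is not certain.** With a strong correlation or an early full effect the F test exceeds 0.80, and the Sidak figures apply only if the post hoc 6-month t-test is the deciding result. This also stands, but the ambiguity is part of the problem: the plan does not say which result decides.
- **The gain depends on r and on what 1.06 measures.** Correct. Section 2.4 does not settle the latter, although Section 2.7.2 defines the outcome as modification of quality of life, which leans towards change. On the follow-up reading the gain at r = 0.3 is small.
- **Pooling the joints would remove most of the deficit.** With 28 completers per arm and the same d, power is 0.97 unadjusted and 0.95 or 0.93 with Sidak over 2 or 3. But Section 2.4 powers each joint separately, so that is a different comparison.

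A reader might also infer that the plan drops everyone with a missed visit, up to 24 of 80 (0.30 × 80). The document does not say so. Listwise deletion is how classical repeated-measures ANOVA usually runs, and it would sit badly with intention to treat, but the article states no missing-data rule and a fuller plan may contain one. The 30% loss was already budgeted in 14/0.70 = 20, and a 6-month ANCOVA also loses anyone without a 6-month score.

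**Conclusion.** The point holds as a mismatch between two stated sections, with an improvement available from data already being collected. The 0.80 belongs to a test that Section 2.8 does not name as primary. Along the planned route, power per joint with 14 completers per arm could be as low as 0.53 (F test, r = 0.3, gradual effect) or 0.60 (Sidak over three comparisons), or as high as 0.96. The baseline-adjusted contrast gives about 0.80 to 0.96 on one reading of the effect size and 0.83 to 0.92 on the other. Within each reading it matched or exceeded the F test in every scenario tried, to within rounding.

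These figures rest on d = 1.06, equal correlations between assessments and r from 0.3 to 0.7, none of which can be checked from the article. It would go too far to say that the planned analysis is invalid, that baseline data go unused, or that adjustment always helps. This should be changed, but it does not undermine the trial.

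**What to change.** Reword Section 2.8 to say:

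- The primary test is the intervention-control difference in the SF-36 physical domain at 6 months, within each joint as powered, at two-sided 0.05 without Sidak correction, adjusted for post-surgery baseline SF-36.
- It is estimated by ANCOVA, or by a mixed model with baseline SF-36, arm, visit and arm-by-visit. The mixed model also keeps participants who have only a 3-month value.
- Sidak correction applies to the 3-month and within-arm comparisons.

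Section 2.4 should also say whether 1.06 refers to change or to the follow-up score. The cost is a few sentences and one degree of freedom per primary comparison, with no additional patients or assessments.

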#### 2.7.3. Secondary Outcomes 

Secondary outcomes are measures which may influence QoL.

Impairments, functional and clinical status.

Maximal strength of the lower limbs can be reliably measured with a hand-held dynamometer [49,50,51,52]. It measures the peak isometric force generated from a muscle group. It is widely used to evaluate the strength of knee [49,50,51] and hip muscles [52,53,54] in healthy elderly and people with osteoarthritis.

Hip and knee joints mobility [55] are measured by goniometry. 

The Hand Grip test will be measured by Hydraulic Hand Jamar Dynamometer. This measure has been strongly associated with frailty in the elderly population [56,57].

Pain is measured by visual analogue scale (VAS) [58,59,60]. VAS is a psychometric response scale widely used for measuring subjective characteristics that cannot be directly measured such as pain. It is widely used to measure pain in orthopedic studies.

Time Up and Go is a valid and reliable test used to examine physical performance and lower extremity [61]. It has been used in several clinical trials concerning different conditions [62,63,64], including arthroplasty [65,66,67,68]. It measures the time to stand from a standard chair, walk to a 3 m distance, turn around and return to sit on the same chair.

Single Stance test [69] is a useful tool for estimating standing balance and discriminating from low to high functional ability in individuals of various ages and functional levels. It is reliable, swift and easy to administer. It measures time subjects can balance on one leg up to a maximum of 30 s.

The 30 s Chair-Stand Test [70,71] is a valid and reliable single-item performance test for assessing lower limb function. It is performed by counting the number of stands completed in 30 s with hands crossed on the chest. 

The Harris Hip Score (HHS) [72] is a disease-specific, instrument widely used as outcome measure after THR. The domains covered are pain, function, absence of deformity and ROM. It has been translated and validated in the Italian language [73]. 

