## Figures and Tables

**Figure 1 ijerph-18-06732-f001:**
[figure not shown]
Study design.

**Table 1 ijerph-18-06732-t001:** Inclusion and exclusion criteria.

Inclusion Criteria	Exclusion Criteria	
Pre-Surgery Criteria	Pre-Surgery Criteria	Post-Surgery Criteria
Signed informed consent; Age: 50–80 years; Indications: Patient with advanced unilateral osteoarthritis requiring primary THR or TKR; General: ASA ^1^ class 1 or 2;	1. Unable/unwilling to sign the informed consent form of the study and/or willing to comply with the study requests; 2. Poor knowledge of Italian language which prevents understanding of the content of the consent form and/or of instructions for assessment and/or training; 3. Severe functional limitations of other lower extremity joints besides that for which surgery is planned; 4. Impairment of communicative and/or sensory functions so severe to make impossible understanding or executing trainer’s instructions (dementia, aphasia, blindness, deafness); 5. Heart failure (NYHA ^2^ class > 2); 6. Unstable angina; 7. Pulmonary disease requiring oxygen therapy; 8. Symptomatic peripheral arteriopathy; 9. Recent myocardial infarction or hospital admission for any other reason in the previous six months; 10. Symptomatic orthostatic hypotension; 11. Hypertension in poor pharmacologic control (diastolic > 95 mmHg, systolic > 160 mmHg); 12. Relevant neurological condition impairing motor or cognitive function; 13. Any other condition that the medical doctor considers contraindicating the participation in an exercise program of moderate intensity; 14. Severe depression	Functional performance: Able to stand and walk > 500 m independently; Pain: score ≤ 4 in VAS ^3^ during rest.

^1^ ASA: American Society of Anesthesiologists; ^2^ NYHA: New York Heart Association Functional Classification; ^3^ VAS: Visual Analogue Scale.

**Table 2 ijerph-18-06732-t002:** Variables collected during the study and time of recording.

	Assessments			
	before Surgery	after Surgery and Rehab		
		Baseline	3 Months	6 Months
General characteristics				
Age	X			
Gender	X			
Body mass index	X			
Comorbid conditions	X			
Education	X			
Social status	X			
Professional status	X			
Home-Gym Distance (only for intervention groups) Possibility to reach the gym in autonomy		X X		
Rehabilitation treatment (duration and number of sessions)		X		
Rehabilitation treatment				
Before surgery (duration and number of sessions)		X		
After surgery (duration and number of sessions)		X		

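### The tests named for non-normal outcomes cannot make the between-arm comparison that Section 2.8 promises

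*Protocol article*

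**What the plan says.** Section 2.8 introduces its outcome tests with a double purpose: "To compare the changes between and within intervention groups and control groups among baseline and follow-up assessments the following tests will be used". Two routes follow. Normally distributed variables go to repeated-measures analysis of variance with Sidak-corrected t-tests. For the rest the text reads: "for non-parametric variables, the Friedman test followed by the Wilcoxon test with Bonferroni correction".

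The same section names one rank test for independent groups, Mann–Whitney, but lists it only among the tests for baseline characteristics.

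Two other places fix what the trial is meant to compare. The hypothesis at the end of the Introduction is that participants in the programme will do better than those under usual care. Section 2.4 sizes the trial, for hip and knee separately, on a "two-code test for independent groups".

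**The concern.** The Friedman test ranks each subject's repeated measurements and asks whether they differ across visits. It contains no term for treatment arm. The usual post hoc test after it is the Wilcoxon signed-rank test between pairs of visits, which is also within-subject. So the tests assigned to the between-arm question on this route answer a different one: did this group change over time?

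That matters because both arms could change for reasons unrelated to the programme. The randomised comparison starts six months after surgery and runs for six more (Section 2.1). The Introduction cites a report of perceived function still improving four years after surgery. Controls receive activity advice and are contacted monthly (Section 2.6.2). A within-arm change does not isolate the programme.

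At least one outcome is a likely candidate for this route. Section 2.7.3 says of the Single Stance test: "It measures time subjects can balance on one leg up to a maximum of 30 s". A ceiling of that kind makes a normal distribution doubtful.

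**Working it through.** **1. The contrast for which the trial was sized.** Inputs from Section 2.4: standardised effect 1.06 ("was found a size effect of 1.06"), α = 0.05, power 0.80 ("a sampling power (1-β) of 0.8"), drop-out 30%. The phrase two-code is read as two-sided, which is an assumption.

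- Per group: n = 2(z₀.₉₇₅ + z₀.₈₀)² / d² = 2(1.960 + 0.842)² / 1.06² = 15.70 / 1.124 = 13.97, so 14.
- With drop-out: 14 / 0.70 = 20, which is the stated figure. Four groups give 80.
- A one-sided test would give 12, and 12 / 0.70 = 17.1, so 18. This does not match.

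The stated size therefore reproduces from an independent-groups, two-sided comparison of intervention with control within each joint.

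**2. What each named test can estimate.**

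| Test in Section 2.8 | Use assigned to it | Has a treatment-arm term? |
|---|---|---|
| Mann–Whitney | Baseline characteristics | Yes |
| Repeated-measures ANOVA | Change, normal outcomes | Can carry group-by-time, though the text does not name that term |
| Friedman | Change, non-normal outcomes | No |
| Wilcoxon after Friedman | Change, non-normal outcomes | No, on the signed-rank reading |

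Only the non-normal route lacks a between-arm test of change.

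**3. What would follow if within-arm significance were read as efficacy.** This was checked by simulation with 2,000 runs per setting. The protocol gives none of the distributional inputs, so these are assumptions: skewed (log-normal) data, three visits, within-subject correlation 0.6, and the same improvement in both arms (half by 3 months, all by 6 months, in SD units on the log scale). There is no treatment effect. An arm counts as significant if Friedman gives p < 0.05 and the baseline-to-6-month signed-rank p-value, multiplied by 3, is below 0.05. The comparator is a two-sided Mann–Whitney test on change from baseline to 6 months. The sizes are the 14 evaluable and 20 enrolled per arm from step 1.

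| Common change (SD) | Intervention arm only, n = 14 | Mann–Whitney, n = 14 | Intervention arm only, n = 20 | Mann–Whitney, n = 20 |
|---|---|---|---|---|
| 0 | 0.9% | 3.8% | 1.1% | 6.0% |
| 0.3 | 5.8% | 4.7% | 8.2% | 4.4% |
| 0.5 | 16.0% | 4.7% | 22.7% | 5.0% |
| 0.7 | 23.2% | 4.0% | 22.9% | 4.5% |
| 1.0 | 14.6% | 4.2% | 5.7% | 3.7% |

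The simulation standard error is about 0.5 points near 5% (√(0.05 × 0.95 / 2000) = 0.0049) and 0.9 points near 23% (√(0.23 × 0.77 / 2000) = 0.0094). The false-finding rate falls again at 1.0 SD because both arms then usually reach significance: the intervention arm does so in 82% of runs at n = 14 and 95% at n = 20. The Mann–Whitney column counts rejections in either direction.

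**The case against.** The strongest defence is that the intention to compare arms is written down. Section 2.8 says so, the hypothesis says so, and the sample size is built on it. That stands. A reader might infer that the trial will conclude from improvement in one arm and not in the other, but the protocol nowhere states such a rule. The supported fault is that the named tests do not carry out the stated aim.

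Second, Wilcoxon is not qualified and could mean the rank-sum test. The ambiguity is real. Signed-rank is nevertheless the natural reading, because the test follows Friedman as its post hoc step and the same section calls the independent-groups test Mann–Whitney. Even on the rank-sum reading, the arm comparison would come only as the follow-up to an omnibus test of time with no treatment factor.

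Third, a reader might infer that the primary outcome has no treatment comparison. The text does not support that. The SF-36 is exposed only if it is judged non-normal. Section 2.4 plans it with a standardised effect and an SD, which suggests that the parametric route is expected, and that route can carry a group-by-time term. Nothing in the protocol says that the SF-36 will be skewed.

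Fourth, the entry limit in Table 1 ("Pain: score ≤ 4 in VAS", at rest) does not show that pain as an outcome will be non-normal. Section 2.7.3 does not say that the outcome is pain at rest, and a limit at entry does not fix the distribution of later values or of changes. Single stance is the firm example.

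Finally, a full analysis plan may exist. That does not answer the point, because Section 2.8 itself assigns these tests to the between-arm comparison. The fault lies in a stated rule and is not an omission.

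**Conclusion.** The point holds in this limited form: on the non-normal route, the tests that Section 2.8 names cannot make the between-arm comparison that it promises and that the hypothesis and sample size need. This rests on reading Wilcoxon as signed-rank. It does not depend on the simulation.

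The reach is conditional. It covers whichever outcomes are judged non-normal, and the primary SF-36 only if it is among them.

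The practical size depends on how the within-arm results would be used. If significance in the intervention arm only were taken as efficacy, the false-finding rate would be about 1% when neither arm changes and about 6% to 23% when both improve equally by 0.3 to 1.0 SD. A between-arm Mann–Whitney test on change stays at about 4% to 6%. The skewness, the correlation of 0.6 and the common improvement are all assumed. The 23% is the top of the range and should not be quoted as the expected rate.

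**What to change.** In Section 2.8, name a between-arm test for non-normal outcomes. Mann–Whitney on change from the post-surgery baseline would be enough, and a baseline-adjusted rank analysis is an alternative. Apply it to THR and TKR separately, in line with the sample size, and make it the basis for any efficacy claim. Keep Friedman and Wilcoxon as within-arm description only, and state that the Wilcoxon test is the signed-rank test.

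The cost is a sentence or two of wording and one simple extra test per outcome, with no new data. If the SF-36 itself were analysed by ranks, some power could be lost. At an assumed rank-test efficiency of 0.955, 14 / 0.955 = 14.7, so 15 evaluable per group, and 15 / 0.70 = 21.4, so 22 enrolled. At a worst case of 0.864, 14 / 0.864 = 16.2, so 17 evaluable, and 17 / 0.70 = 24.3, so 25 enrolled.
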